#### Initiating treatment

If the blood glucose level is >4.0 mmol/l and the baby is receiving a minimum glucose infusion of 4 mg/kg/min (60 ml/kg/d of 10% dextrose) then the *fixed dose insulin infusion *regimen will be started. If the blood glucose is <4.0 mmol/l then 20% dextrose will be infused and blood glucose rechecked within one hour, repeatedly increasing 20% dextrose and checking BG hourly until BG is >4.0 mmol/l. Only when the BG is >4.0 mmol/l will the fixed dose insulin infusion be started. Once the insulin infusion has started the BG will be checked hourly until stable and then 2 hourly increasing to a time interval of 4 hours. If a baby is stable the time interval may be increased to a maximum of 6 hours under the guidance of the Principal Investigator. The fixed dose insulin infusion will start within 24 hours of delivery and will run for seven completed days. The fixed dose insulin infusion will be infused via the same line that the baby is receiving its main source of dextrose/parenteral nutrition. This will ensure that if there is a break in the delivery of the main source of dextrose to a baby that there will also be a simultaneous break in the infusion of insulin.

The *fixed dose insulin infusion *will be maintained but any decisions regarding a baby's maintenance glucose infusions and fluid requirements will be taken by the medical team caring for the baby. If there are any clinical changes in the rate of glucose being infused or a clinical insulin infusion is started then a blood glucose will be rechecked hourly until stable.

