##### Hypoglycaemia

If the blood glucose level falls <4.0 mmol/l, intravenous lines should be reviewed and additional 20% dextrose infused to avoid hypoglycaemia – starting at 1 ml/kg/hour extra (see Figure 1). A review should be made of the amount of dextrose being received and the additional 20% dextrose infusion that has been prepared should be titrated to prevent hypoglycaemia. Repeated BG measurements should be taken hourly repeatedly increasing the 20% dextrose until the value is stable and >4.0 mmol/l. This should prevent BG levels falling to <2.6 mmol/l. However if BG < 2.6 mmol/l then the insulin infusion should be stopped, all lines checked to ensure the baby is receiving the dextrose prescribed and additional 20% dextrose infused. A repeat BG should be taken after 60 minutes, and hourly with the 20% dextrose repeatedly increased to maintain the BG 4.0–8 mmol/l. Close liaison with the medical and nursing staff is critical to make sure they understand the treatment algorithm and that the study is aiming to control the BG between 4–8 mmol/l. They must be aware of the importance of taking regular and frequent BG measurements to ensure euglycaemia and that 20% dextrose should be started if a BG level is recorded that is <4.0 mmol/l.

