### B. Babies randomised to control arm

As is usual practice initial management will involve obtaining intravenous access, measuring blood glucose and initiating a dextrose infusion.

*Study control babies will in addition require*

i) Insertion of a *MiniMed *sensor (subcutaneous insertion in the thigh, as described above).

ii) Blood Glucose control as per standard clinical protocol

Blood glucose control

These babies will receive standard clinical care.

Therefore if BG:

<2.6 mmol/l standard unit management of hypoglycaemia

>10 mmol/l if 2 or more readings are >10 mmol/l consider addition of insulin infusion

Once BG has fallen to <10 mmol/l then any insulin infusions should be stopped.

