### Measurement of outcomes

#### Primary outcomes

Death on or before expected date of delivery (taken as date considered the most accurate estimate of delivery date).

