### Statistics

Intention to treat analyses will be performed comparing the outcome of all infants allocated to early insulin treatment compared to those allocated placebo, regardless of how complete treatment was. Statistical analyses will use standard methods to calculate the event rates, time-to-event rates, relative risks, and numbers needed to treat for each outcome in the treatment compared with placebo group, along with 95% confidence intervals. Where appropriate χ2, Fisher's exact or log rank tests of significance will be performed and presented with p-values.

The primary outcome will be modelled with logistic regression in order to evaluate a 95% confidence interval for odds ratio according to treatment group adjusted for key prognostic variables, including if significant, geographic centre. No formal interim analyses are intended although the trial's Data Monitoring Committee (DMC) will meet regularly, have access to unblinded data and would recommend early termination to the Trial Steering Committee ifjudged appropriate based on ethical, safety or efficacy considerations. Time to event analyses stratified by category of birthweight, using Kaplan-Meier survival analyses and stratified logrank tests will be used to assist DMC decision-making. For the secondary outcomes, modelling with either multiple regression (for continuous variables) or logistic regression (for binary variables) will be employed, adjusting for the same baseline covariates as the primary analysis. If individual terms in models are non-significant at level 0.05, then simpler models may be presented instead.

A secondary analysis will be on an "as treated" basis, defining treatment exposure as at least 4 days without interruptions of more than 1 hour.

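### The secondary as-treated definition requires 4 days of infusion, so when applied to mortality it excludes early insulin-arm deaths from the exposed group and favours insulin

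*Protocol article*

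**What the plan says.** The Statistics section puts intention to treat first: "Intention to treat analyses will be performed comparing the outcome of all infants allocated to early insulin treatment", however complete their treatment was. It then adds one sentence on a secondary as-treated analysis, "defining treatment exposure as at least 4 days without interruptions of more than 1 hour". That sentence does not name the outcomes to be analysed. It does not say whether insulin-arm infants who miss the definition are counted with the controls or left out. It sets no survival condition for the comparison group.

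Under Primary outcomes the endpoint is "Death on or before expected date of delivery", with no lower limit on the time of death. Under Initiating treatment, "The fixed dose insulin infusion will start within 24 hours of delivery and will run for seven completed days".

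Two passages bear on who meets the definition. Under Hypoglycaemia: "However if BG < 2.6 mmol/l then the insulin infusion should be stopped", followed by "A repeat BG should be taken after 60 minutes" and hourly checks. In the control arm, insulin may be given for repeated high readings, but "Once BG has fallen to <10 mmol/l then any insulin infusions should be stopped".

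**The concern.** Exposure is decided by what happens after randomisation, and the outcome can occur while it is still being decided. To be exposed, an infant must live long enough to receive 4 days of infusion. A control infant faces no such requirement. Every insulin-arm death before that point leaves the exposed numerator, while control deaths in the same days all count. The exposed group has a guaranteed survival period that has nothing to do with insulin.

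At stake is a pre-specified mortality comparison that could show a benefit from an inert treatment, and that could be set against a null or unfavourable intention-to-treat result.

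**Working it through.** **Inputs from the article (Power calculation).** Mortality 20% by expected date of delivery, target difference 10 percentage points, 80% power, 5% significance, 428 infants needed, 500 to be recruited.

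**The plan's own figure.** For 20% against 10%, the normal approximation gives 199 per arm (398), or 219 per arm (438) with continuity correction. At 214 per arm, two-sided Fisher's exact test has 80.1% power, so 428 is reproduced. The as-treated definition does not enter that calculation.

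**Assumptions not in the article.** 1:1 allocation (250 per arm); a share f of deaths falling before 4 days of infusion can be completed, varied from 5% to 40%; and a disqualifying interruption in 20% of insulin-arm infants alive at that point, unrelated to outcome. No treatment effect.

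**Expected values.**
- Early death risk: e = 0.20 × f.
- Mortality among infants alive at day 4: (0.20 − e)/(1 − e).
- Exposed infants: 250 × (1 − e) × 0.80.
- Unexposed infants counted as untreated: comparison group = 500 − exposed, with 100 − exposed deaths.
- Unexposed infants dropped: comparison group = 250 controls with 50 deaths (20%).

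Worked for f = 30%: e = 0.06, so 15 of 250 insulin-arm infants die early and 235 remain, with 35 later deaths (35/235 = 14.9%). After interruption, 235 × 0.80 = 188 are exposed, with 28 deaths (14.9%). Counted as untreated: (100 − 28)/(500 − 188) = 72/312 = 23.1%, risk ratio 0.65. Dropped: 14.9% against 20%, risk ratio 0.74.

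The last two columns are simulated two-sided rates of p < 0.05 (two-sample z-test; the choice of simulation run moves them by about a point).

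| Share of deaths before day 4 | Exposed | Comparison, counted as untreated | RR, counted as untreated | RR, dropped | False significance, counted as untreated | False significance, dropped |
|---|---|---|---|---|---|---|
| 5% | 38/198 = 19.2% | 62/302 = 20.5% | 0.93 | 0.96 | about 6% | about 6% |
| 10% | 36/196 = 18.4% | 64/304 = 21.1% | 0.87 | 0.92 | about 11% | about 7% |
| 20% | 32/192 = 16.7% | 68/308 = 22.1% | 0.75 | 0.83 | about 31% | about 14% |
| 30% | 28/188 = 14.9% | 72/312 = 23.1% | 0.65 | 0.74 | about 61% | about 28% |
| 40% | 24/184 = 13.0% | 76/316 = 24.1% | 0.54 | 0.65 | about 87% | about 48% |

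**Role of interruption.** Random interruption does not create the bias. With no interruption, false benefit (nominal 2.5% in that direction) is 43% (counted as untreated) or 15% (dropped) at f = 20%, and 77% or 32% at f = 30%. With f = 0 and 10% of infants interrupted, the result depends on who they are:
- Same mortality as the rest: risk ratio 1.00.
- Twice the mortality: 0.91 (dropped) or 0.85 (counted as untreated).
- Half the mortality: 1.05 or 1.10.

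**Controls who received insulin.** If 5% to 20% of controls alive at day 4 were classed as exposed, with one to three times the mortality of the rest, the risk ratio at f = 30% (unexposed counted as untreated, no interruption) stays between 0.56 and 0.77.

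**After the change.** Requiring survival to day 4 in both arms gives, at f = 30%, 28/188 = 14.9% against 35/235 = 14.9%, risk ratio 1.00.

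**The case against.** The strongest reply is that nothing decisive rests on this analysis. It is one sentence, labelled secondary, beneath a clear intention-to-treat commitment. That stands: a reader might infer that the trial's main mortality result is compromised, and the article does not support that.

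The size is also open. The article gives no timing of deaths. It excludes major anomalies and infants for whom continuing intensive care is under discussion, which plausibly removes some early deaths. At a 5% share the false-significance rate barely exceeds nominal. A reader might take it as given that unexposed insulin infants join the controls; the text does not say so, and dropping them roughly halves the error rates at shares of 20% and above. Nor is mortality named as the as-treated outcome. For glucose or biomarker outcomes, a duration-based definition is more natural.

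A reader might also infer that the stop for low glucose systematically moves hypoglycaemic infants out of the exposed group and adds to the bias. The text does not establish this. A stop of exactly 60 minutes is within the one-hour limit, and the article does not say when insulin restarts. A 4-day run could come before or after a stop within the 7 days, and the dextrose step is expected to prevent such lows. Reclassification is possible, but it adds bias towards insulin only if interrupted infants die more often, which the documents do not show.

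What remains is the survival requirement. It follows from the stated definition and does not depend on any of these points.

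**Conclusion.** The concern holds for the as-treated analysis when applied to mortality. Any insulin-arm death before 4 days of infusion biases the comparison towards insulin, whether unexposed infants are dropped or counted as untreated. The direction of this component follows from the definition. Its size rests on an assumed early-death share: negligible at 5%, and at 30% a spurious difference of about 5 points (14.9% against 20%) to 8 points (14.9% against 23.1%), against a design target of 10 points. Selection by interruption could add to this or offset part of it; the documents do not settle which. The intention-to-treat analysis and the sample size stand. This should be fixed, but it does not threaten the primary conclusion.

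**What to change.** For mortality, do not use the 4-day definition without a landmark. Restrict the as-treated comparison to infants in both arms alive at day 4, or model exposure as time-dependent. Fix the landmark at a set time from randomisation by which 4 days of infusion can have been completed, and classify exposure only on what has happened by then. A run completed later would bring the survival requirement back.

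State whether insulin-arm infants who miss the definition are dropped or counted with the controls, how controls who received insulin are classified, and which outcomes the analysis covers. Label the result descriptive, because a landmark does not remove selection by interruption.

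A complier-average estimate using allocation as the instrument could be added as an option. If exposure there means starting study insulin, it answers a different question from sustained exposure, and it will sit close to intention to treat if nearly all allocated infants start.

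The cost is wording and a little analysis work. The landmark estimate excludes early deaths and is less precise, so it cannot stand in for the intention-to-treat result.

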### Power calculation

Sample size is based on the primary outcome variable of mortality. This is based on statistical power analyses for mortality of 20% by EDD. To predict an absolute difference of 10% with 80% power at the 5% level of significance we would need 428 patients. Non-compliance is not likely to be a problem, although withdrawal from treatment may be 5–10%. Thus we aim to recruit 500 patients. Each unit has an admission rate of approximately 100 very low birth weight babies per year. Due to the confined period of recruitment being within 24 hours of delivery we predict 50% availability for recruitment (some babies will be transferred in after delivery). Coupled with an estimated 60% rate of consent we predict we would recruit 500 infants over a 2 year period with a realistic safety margin. For the primary outcome measure of mortality by EDD loss to follow up should be negligible.

### Ethical and regulatory issues

#### Patient information and consent

Parents will be given full verbal and written information regarding the objective and procedures of the study and the possible risks involved. If possible parents will be approached prior to delivery to allow time for considering study details prior to giving assent. However all parents would be asked to confirm informed consent in writing after a baby's birth. As patients need to be recruited within 24 hours of delivery, a system of continuing consent will be used over the first 3 days to ensure that parents are happy with the decision to consent to their baby's participation in the study.

### Regulatory bodies

EUDRACT Number: 2004-002170-34

MHRA: DDX granted 21/4/04 became a CTA 1/4/04

UK Sponsor Cambridge University Hospital NHS Foundation Trust

### Study timetable

The study started in Cambridge in January 2005 following confirmation of final protocol approval by ethics committees and MHRA regulatory approval. New study centres were then taken on over the subsequent 12 months and recruitment is currently on target to be completed by December 2007. All laboratory analyses will be completed within 6 months of the last patient recruited.

## Discussion

This study is based on the hypothesis that early intervention with insulin replacement prevents catabolism and the hyperglycaemia seen during the first week of life, in the VLBW preterm infant. The strategy is not simply that used in adult intensive care to actively titrate insulin in subjects with hyperglycaemia, although the adult outcome data particularly with respect to reductions in sepsis, with tight glycemic control, may have interesting parallels. Our approach, to administer continuous insulin with glucose cover also provides additional safety compared to sliding scales of insulin generally used in this population, and also highlights the differences with adult ICU protocols. Although mortality and morbidity rates are much lower in infants 1–1.5 kg compared to those <1 Kg it was felt that these infants may well benefit from any long term effect on growth and/or reduction in the incidence of retinopathy and therefore they have been included in the protocol.

## Summary

Very low birth weight infants requiring intensive care have relative insulin deficiency often leading to hyperglycaemia during the first week of life which has been associated with increased mortality and morbidity. The physiological influences on insulin secretion and sensitivity, and the potential importance of interventions to improve glucose control at this time are not well established. However theoretically, improved insulin delivery and restoration of IGF-I levels could have important implications for short term survival as well as the long term outcomes of these VLBW babies. This is a multi-centre, randomised controlled trial of early insulin replacement in VLBW babies. Babies will be randomised to receive a continuous insulin infusion (0.05 units/kg/h) with 20% dextrose support or to receive standard neonatal care for the first 7 days of life. The primary end point will be mortality on or before expected date of delivery, secondary end points will be markers of morbidity and include episodes of sepsis, severity of retinopathy, chronic lung disease and growth.

## Abbreviations

IGF-I insulin like growth factor one

IGFBP-1 insulin like growth factor binding protein one

VLBW very low birth weight

BAPM British Assocoation of Perinatal Medicine

CGMS continuous glucose monitoring sensor

BG blood glucose

DMC Data Monitoring Committee
